#### 2.1.2. Inclusion Criteria

-Age 18 years or older.-Chronic severe ischemic and non-ischemic mitral regurgitation (EROA ≥ 0.4 cm echocardiogram) with tethering as a major mechanism.-The occurrence of symptoms that indicate secondary mitral regurgitation (3+ or 4+ as determined by echocardiographic laboratory assessment) as an outcome of the development of cardiomyopathy, whether of an ischemic or non-ischemic etiology.-The management of the subject was conducted in accordance with the relevant clinical guidelines, including those pertinent to CAD, LV functional impairment, MR, and HF.-The procedure was conducted using either a standard surgical approach or a transcatheter technique for mitral valve repair.-Patients with atrial functional mitral regurgitation.-CAD in patients who underwent an S-MVi, with or without the need for coronary revascularization.-It will fall upon the cardiac team at each center to ascertain which patients to include in the register. The choice of treatment will be dependent on whether the patient received a standard surgical approach or a transcatheter technique for mitral valve repair.-In order to be included in the TEERMISO registry, it will be necessary for the individual in question to possess the capacity to sign both the informed consent and the Medical Information Release forms.

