#### 2.2.2. Secondary

A number of secondary endpoints will be subjected to evaluation in the context of the forthcoming trial. The trial will evaluate the primary secondary endpoint, which is all-cause mortality. This endpoint offers supplementary clinical data to the primary physiological endpoint, enabling an evaluation of the overall efficacy of the treatment. Moreover, the subsequent secondary endpoints have been delineated for the trial.

▪Functional Status, Hospitalizations, and Neurocognition.NYHA classification.MACE (death, stroke, worsening heart failure (+1 NYHA Class), CHF hospitalization, mitral valve re-intervention).Angina class.Neurocognitive results.Peak VO2 (assessed by a cardiopulmonary stress test).The rates of patients readmitted within 30 days and the long-term readmission rates for all patients, as well as for those with cardiovascular issues and heart failure, are to be determined. Furthermore, the proportion of days spent outside of the hospital setting during the follow-up period following survival will be determined.LOS for the hospital stay and discharge destination.
▪Physiologic Measures.Echocardiography assessment.Quantification of MR, specifically the effective regurgitant orifice area (ERO).Quantifying mitral valve area.LV size, function, and geometry (including LVEF, LVEDD, LVESD, LVEDVI, LVESVI, and LV sphericity).Assessment of mitral valve and subvalvular structures.LA dimension.RV size and function.MV tethering.Assessing regional wall motion for left ventricular function and viability.Appropriate revascularization.▪Safety.
Incidence of serious adverse events.Reoperation for MR and freedom from reoperation in general.▪Perioperative Measures.Operative time for each procedure. For the standard surgical mitral valve operation, cardiopulmonary bypass (CPB) and cross-clamp time are required.Blood loss and transfusion.▪Quality of Life and Economic Measures.
Change in quality of life (QOL).Minnesota Living with Heart Failure (MLHF) score.SF-12.EuroQoL.Dasi.

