In contrast, functional status will be assessed by measuring maximal oxygen uptake (VO2 peak), which will be determined by conducting cardiopulmonary exercise testing at predefined intervals in patients who do not have any clinical indications that would preclude the performance of exercise testing (e.g., unstable angina or left main disease). A uniform verbal prompting protocol will be employed to encourage all patients to exercise to the point of voluntary exertion. The incorporation of Borg’s CR10 RPE (rate of perceived exertion) will be beneficial in subjects who are unable to achieve an RER (respiratory exchange ratio) of ≥1.0, providing an additional measure of the level of exertion. Accordingly, the rating of perceived exertion (RPE) will be evaluated and documented at two-minute intervals for all subjects using the RPE scale, which ranges from 0 to 10. The RPE scale will be used in all tests conducted as part of this study, and patients will be provided with laminated cards illustrating how to use the scale during these tests. A standardized protocol will be employed for the performance of cardiopulmonary exercise testing, and the results will be evaluated by the cardiologist assuming responsibility for the case at the respective enrolment center.

▪Neurocognition.

The aim of this research is to undertake a comparative analysis of the neurocognitive profiles of the treatment groups, employing a battery of tests to assess their cognitive performance. The tests used in this study include the Hopkins Verbal Learning Test, Trail making Tests A and B, MCG Complex Figures, Boston Naming Test, Digit Span, and Digit Symbol Substitution. Neuropsychologists, whose training was conducted by experienced professionals at each recruitment site, will administer the aforementioned neurocognitive tests. The responsibility for scoring the neurocognitive tests will be borne by the neurologists at each center of enrolment.

▪Hospitalization.•Index hospitalization.

The length of stay for the index hospitalization will be quantified and disaggregated by days spent in the ICU. Furthermore, the discharge location will be recorded.

▪Readmission.

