The readmission rate will be calculated for the first 30 days after the procedure and for the entire follow-up time. All admissions will be classified, including those related to cardiovascular disease and HF. For a readmission to be considered heart failure-related, at least two of the following signs and conditions of acute decompensated heart failure must be present:Dyspnea felt related to HF.Administration of vasodilators, intravenous diuretics, or inotropes.Pulmonary capillary wedge pressure (PCWP) or LVEDP > 18 mmHg.On physical assessment, rales may suggest the existence of pulmonary edema or pulmonary vascular congestion. This may be seen on radiographs.

All readmissions will be categorized by the investigating physician and adjudicated by the attending cardiologist.

▪Days Spent Alive and Outside of the Hospital.

To assess the total number of days alive and out of the hospital between treatment groups, a pooled analysis will be performed. Additionally, the proportion of days spent out of the hospital in proportion to the total number of days spent alive following the procedure will be quantitatively evaluated.

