A total sample population of 630 patients was calculated as sufficient to detect a significant difference in the rate of reverse left ventricular remodeling, with 384 patients undergoing surgical mitral valve repair and 246 patients undergoing transcatheter mitral valve repair. This study was powered at 80% with a two-tailed alpha level of 0.05. In order for a *p*-value to be deemed statistically significant, it must be less than 0.05. All statistical analyses were performed with the aid of the R software package developed by the R Foundation for Statistical Computing in Vienna, Austria.

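### The 30-day readmission rate is counted from the procedure, so if index stays differ between surgery and TEER, the longer-stay arm has fewer days at risk and a lower rate at equal post-discharge risk

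*Protocol article*

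**What the plan says.** Section 2.2.2 lists the endpoint without a starting point: "The rates of patients readmitted within 30 days and the long-term readmission rates for all patients". Section 2.3, under Readmission, supplies one: "The readmission rate will be calculated for the first 30 days after the procedure and for the entire follow-up time". Nothing elsewhere in the article moves the start to discharge, takes out the days of the index stay, or expresses the 30-day figure per day at risk.

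The same section records the index stay: "The length of stay for the index hospitalization will be quantified and disaggregated by days spent in the ICU". Discharge location is recorded too. It also defines days alive and out of hospital, and a version relative to survival time: "the proportion of days spent out of the hospital in proportion to the total number of days spent alive following the procedure".

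The groups compared are standard mitral surgery, for which bypass and cross-clamp times are collected, and TEER. Section 3 plans Lasso variable selection, propensity-score weighting and a doubly robust regression. It gives the group sizes as 384 surgical and 246 transcatheter patients, in a calculation for left ventricular remodeling. The article states no expected index stay and no expected readmission risk for either group.

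**The concern.** The procedure is a natural time zero for death or MACE, which can occur from day 0. Readmission cannot occur until the patient has left hospital. A fixed window from the procedure therefore gives each patient a different number of days at risk, and that number depends on the index stay, which is itself an outcome of treatment. A patient still in hospital on day 30 enters the 30-day figure as not readmitted, so a long, complicated stay counts in that figure as a good result.

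The planned weighting and regression balance characteristics measured before treatment. Index stay comes after treatment and the distortion sits in the outcome definition, so adjustment for baseline covariates does not remove it. What is at stake is a 30-day difference between surgery and TEER that partly reflects length of stay, with the sign reversed, but would be read as a difference in readmission risk.

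**Working it through.** The article gives no figure for this endpoint, so there is nothing to reproduce. The question is what the stated clock does when the risk after discharge is the same in both arms.

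**Inputs from the article:** a 30-day window from the procedure (section 2.3); group sizes of 384 and 246 (section 3).

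**Assumed inputs, not in the article:** index stays L of 3 to 14 days; a daily hazard h after discharge, or equivalently a 30-day risk R counted from discharge, with h = -ln(1 - R)/30.

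**Formula, constant hazard:** days at risk = 30 - L, and P(readmitted within 30 days of the procedure) = 1 - exp(-h(30 - L)).

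**Central illustration, h = 0.005, stays of 10 and 3 days:**
- Longer stay: 1 - exp(-0.005 × 20) = 9.5%
- Shorter stay: 1 - exp(-0.005 × 27) = 12.6%
- Ratio 0.0952/0.1263 = 0.75
- Counted from discharge: 1 - exp(-0.005 × 30) = 13.9% in both arms

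For h between 0.003 and 0.008 the 10 vs 3 day ratio stays at 0.75 to 0.76.

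**Range over assumed stays, R from 10% to 25%:**

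| Stays (days) | Days at risk | Difference (points) | Ratio, longer/shorter stay |
|---|---|---|---|
| 7 vs 7 | 23 vs 23 | 0 | 1.00 |
| 7 vs 3 | 23 vs 27 | 1.3 to 3.0 | 0.86 to 0.87 |
| 10 vs 3 | 20 vs 27 | 2.3 to 5.4 | 0.75 to 0.77 |
| 14 vs 3 | 16 vs 27 | 3.6 to 8.6 | 0.60 to 0.62 |

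**Shape of the hazard.** Suppose instead that risk is concentrated soon after discharge: Weibull with shape 0.7, R = 15%, so that P = 1 - exp(-((30 - L)/s)^0.7) with s = 30/(-ln 0.85)^(1/0.7) = 402.
- 10 vs 3 days: 11.5% vs 14.0%, ratio 0.82
- 14 vs 3 days: 9.9% vs 14.0%, ratio 0.71

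The effect is smaller than under a constant hazard, in the same direction.

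**Chance of a misleading significant result.** This is a normal-approximation two-proportion test at two-sided 0.05, with the further assumption that the group of 384 has the longer stay. With a constant hazard and no true difference after discharge, the chance of significance in favor of that group is 19% to 38% for 10 vs 3 days and 42% to 78% for 14 vs 3 days, over R from 10% to 25%. The nominal value is 2.5%.

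**Does the discharge clock repair it?** If hazard depends on time since discharge, yes: each arm has 30 days at risk and equal hazards give equal rates. If hazard declines with time since the procedure, only in part. Take a hazard c·exp(-t/20), with t in days from the procedure, the same curve in both arms, and c = 0.0112 set so that the 3-day arm has 13.9% from discharge:
- Discharge clock, days 10 to 40 vs days 3 to 33: 10.0% vs 13.9%, ratio 0.72
- Procedure clock, days 10 to 30 vs days 3 to 30: 8.2% vs 13.3%, ratio 0.62

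**Long-term readmission.** A 7-day difference in stay over ten years is 7/3,650 = 0.2% of the time at risk.

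**The case against.** The strongest case on the other side has four parts.

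*The consequence is small.* Readmission is one of many secondary endpoints. The primary endpoint is LVEDVI at 10 years and the main secondary endpoint is all-cause mortality. The power statement concerns remodeling. Length of stay, readmission over full follow-up and days alive out of hospital are all reported, and the last of these charges a longer index stay to the arm that has it. This stands and limits the weight of the point. It does not make the 30-day comparison itself correct.

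*The size is assumed.* This also stands. The article gives no stays and no hazards, the ratio depends on the shape of the hazard, and equal stays give no distortion. A reader might infer that surgery is the arm that benefits. That may be a reasonable expectation, but no figure in the article supports it, so the point is conditional on stays differing.

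*The discharge clock is not neutral.* It restricts the analysis to patients discharged alive, a post-treatment group that may differ by arm and is no longer the cohort balanced by the weights. If risk falls with time since the procedure, it closes only part of the gap. Counting from the procedure keeps one time zero and the full cohort. This stands as a cost of the fix and as a reason to keep the procedure-anchored figure as a supplementary description.

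*The wording leaves room.* Section 2.2.2 gives no starting point, and a rate per day at risk would remove the unequal exposure. But section 2.2.2 speaks of patients readmitted, which reads most naturally as a proportion, and section 2.3 names the procedure as the start. The article fixes the clock; it has not simply been left to an analysis plan.

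**Conclusion.** The point holds in conditional form. Followed as written, the 30-day readmission comparison gives fewer days at risk to whichever arm has the longer index stay, and a lower rate at equal post-discharge risk. For assumed stays of 10 vs 3 days the ratio is about 0.75 under a constant hazard and 0.82 under a hazard concentrated soon after discharge. It is nearer 1 for smaller differences in stay and exactly 1 for equal stays. A real difference in post-discharge risk could add to the effect or offset it.

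Three stronger readings are not supported:
- Long-term readmission is not materially distorted; the effect there is about 0.2% of the time at risk.
- A patient in hospital on day 30 is not lost for good. Only the 30-day figure misses a later readmission; the full-follow-up measure can still capture it.
- The primary endpoint and the mortality comparison are untouched.

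This is a worthwhile correction to one secondary endpoint.

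**What to change.** In section 2.3, Readmission, define the 30-day comparison as readmission within 30 days of index discharge among patients discharged alive, with death after discharge as a competing event. State the same starting point in section 2.2.2. Show in-hospital death, index length of stay and days alive out of hospital beside the result. The figure counted from the procedure may stay as a supplementary description. Leave the long-term readmission clock as it is.

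The cost is about one sentence in the definition. Length of stay and discharge location are already recorded, so the discharge date should be derivable without new data. The price in interpretation should be stated with the result: the comparison conditions on discharge alive, which may differ by arm, and it may not fully equalise the arms if readmission risk declines with time since the procedure.

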## Abstract

**Background:** Secondary mitral regurgitation (SMR) is characterized by a pathological process impacting the left ventricle (LV) as opposed to the mitral valve (MV). In the absence of structural alterations to the MV, the expansion of the LV or impairment of the papillary muscles (PMs) may ensue. A number of technical procedures are accessible for the purpose of determining the optimal resolution for MR. Nevertheless, there is a dearth of rigorous data to facilitate a comparative analysis of MV replacement, MV repair (including subvalvular repair), and transcatheter mitral valve interventions (TMV-Is). The objective of this investigation is to evaluate and compare the efficacy and clinical outcomes of transcatheter mitral valve repair (TMV-r) utilizing the edge-to-edge mitral valve repair (TEER) procedure in comparison to conventional surgical mitral valve interventions (S-SMVis) in patients with secondary mitral regurgitation. **Methods and analysis:** A consortium of five cardiac surgery institutions from four European states and Japan have joined forces to establish a multicenter observational registry, designated TEERMISO. Patients who underwent technical procedures for SMR between January 2007 and December 2023 will be enrolled consecutively into the TEERMISO registry. The investigation team evaluated the comparative efficacy of replacement and repair techniques, utilizing both the standard surgical methodology and the transcatheter intervention. The primary clinical outcome will be the degree of left ventricular remodeling, as assessed by the left ventricular end-diastolic volume index, at 10 years. The forthcoming research will assess a variety of secondary endpoints, among which all-cause mortality will be the primary endpoint. Subsequent assessments will be made in the following order: functional status, hospitalization, neurocognition, physiological measures (echocardiographic assessment), occurrence of adverse clinical incidents, and reoperation. **Ethics and dissemination:** The multicenter design of the database is anticipated to reduce the potential for bias associated with institutional caseload and surgical experience. All participating centers possess an established mitral valve protocol that facilitates comprehensive follow-up and management of any delayed mitral complications following replacement surgery or surgical repair of the secondary mitral regurgitation. The data collected will provide insights into the impact of diverse surgical approaches on standard mitral valve surgery and TEER. This will facilitate the evaluation of LV remodeling over the course of long-term post-procedural follow-up. **Trial Registration:** ClinicalTrials.gov ID: NCT05090540; IRB ID: 202201143

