## 2. Methods and Analysis

The TERMISIO prospective observational registry encompasses individuals who have been subjected to technical procedures and treatments for SMR at five cardiac surgery centers located in two European nations (France and Italy) and Japan (Table 3) over the course of nine years, from 1 January 2014 to 31 March 2023. The objective of this study is to collate data on patients who had undergone treatment during the specified period.

The goal is to obtain additional data for the purpose of future clinical research on the topic in question. The data pertaining to the successive patients with SMR will be compiled in an Access database created using Microsoft Access software, developed by Microsoft in its Redmond, Washington, USA, headquarters. The data sheet will comprise a set of predetermined variables, including those pertaining to the baseline, surgical procedure, and postoperative course of the patients. Prior to the commencement of this study, permission will be sought from the relevant institutional review board or local ethical committee in accordance with the legislation of the country in which this study is to be conducted.

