#### 2.2.1. Primary

The primary endpoint of this study is the degree of LV remodeling as assessed by the Left Ventricular End-Diastolic Volume Index (LVEDVI) at the 10-year follow-up.

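### The days-out-of-hospital proportion divides by days alive, so days lost to death carry no penalty and an early death can outscore long survival

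*Protocol article*

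**What the plan says.** The protocol article defines two measures in Section 2.3, under Days Spent Alive and Outside of the Hospital.

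- **A total:** "To assess the total number of days alive and out of the hospital between treatment groups, a pooled analysis will be performed". No time horizon is given.
- **A proportion:** days out of hospital, taken "in proportion to the total number of days spent alive following the procedure".

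The endpoint list in Section 2.2.2 words the second measure differently: "the proportion of days spent outside of the hospital setting during the follow-up period following survival will be determined". That phrase does not settle the denominator; Section 2.3 does.

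Two entry windows appear. Section 2 has patients treated "over the course of nine years, from 1 January 2014 to 31 March 2023"; the Abstract has "between January 2007 and December 2023". The 10-year time point belongs to the primary endpoint, "as assessed by the Left Ventricular End-Diastolic Volume Index (LVEDVI) at the 10-year follow-up", and in Section 4.1 to LVEF and mortality. It is not attached to days out of hospital. No data cut-off date and no entry dates by arm are given.

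All-cause mortality is the main secondary endpoint, and death is a component of MACE. Section 4.1 describes a setting with 50% mortality, without a time point.

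**The concern.** A measure of days alive and out of hospital is normally meant to count death as lost time. Once the denominator is days alive, the alive part drops out: what remains is the share of a patient's survival spent outside hospital. Survival after the procedure is itself an outcome of treatment, so weighting on baseline covariates (Section 3) cannot repair the ratio.

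At stake is the reading of a between-group comparison in a population where the authors themselves expect high mortality. An arm with worse survival could look equal or better on this endpoint, and a reader could take that for benefit.

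The total does penalise death when patients are followed equally long. Its weakness is different and conditional: without a horizon, a patient's attainable total depends on when he or she was treated.

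**Working it through.** The article states no figure for this endpoint, so there is none to reproduce. Hospital days, index stay, survival shape and cut-off below are assumptions for illustration.

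**1. Two patients.** Ratio as defined = (days alive − hospital days) / days alive. Fixed 5-year version = (days alive − hospital days) / 1826.

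| Patient | Ratio as defined | Fixed 5 years |
|---|---|---|
| 3 hospital days, dies at home on day 30 | 27/30 = 90% | 27/1826 = 1.5% |
| Alive at 5 years, 250 hospital days | 1576/1826 = 86% | 1576/1826 = 86% |

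**2. When an early death scores better.** A patient with an index stay of s days who dies at home on day t, without readmission, scores 1 − s/t. A survivor who spends a fraction h of the time in hospital scores 1 − h. The death scores higher when t > s/h. With s = 10, that is after day 333, 200 or 100 for h = 3%, 5% or 10%. The reverse also occurs: with a 10-day stay, a death on day 30 scores 20/30 = 67%, below the survivor's 86%, and a patient who dies on day 20 without leaving hospital scores 0%.

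**3. Two groups.** Assume exponential survival over 10 years (3652.5 days), 10 index days, and hospital time afterwards as a fixed share of days alive. The 50% mortality of Section 4.1 is taken as 10-year mortality. Mean days alive = 365.25 × (1 − S)/λ, with S the 10-year survival and λ = −ln(S)/10. Group ratio = total days out / total days alive.

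- Group A, 50% mortality, 3% in hospital: days alive 365.25 × 0.50/0.0693 = 2635; hospital days 10 + 0.03 × 2625 = 89. Ratio 96.6%; fixed horizon (2635 − 89)/3652.5 = 69.7%.
- Group B, 65% mortality, 2% in hospital: days alive 365.25 × 0.65/0.1050 = 2262; hospital days 10 + 0.02 × 2252 = 55. Ratio 97.6%; fixed horizon (2262 − 55)/3652.5 = 60.4%.

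The ratio prefers B and the fixed horizon prefers A. If B also spends 3% in hospital, its hospital days are 10 + 0.03 × 2252 = 78, its ratio 96.6% and its fixed-horizon value 59.8%. The ratio then hardly registers 15 percentage points of excess mortality.

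**4. The total.** For any common cut-off, first and last entrants differ in potential follow-up by the whole entry window: 9.24 years (Section 2) or 17.0 years (Abstract), unless follow-up is truncated at a common horizon. The relative spread depends on the cut-off. With an assumed 31 December 2023 and the Section 2 window, potential follow-up runs from 0.75 to 10.0 years, a 13-fold range. If every patient is followed to 10 years and truncated there, the range vanishes.

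Identical exponential survival (50% dead at 10 years) was simulated for arms of 384 and 246, with uniform entry and potential follow-up of 0.75 to 10 years. The outcome was days alive.

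- Same entry mix in both arms: false-positive rate 5.4%, so no bias, although potential follow-up explains about 48% of the variance.
- One arm with 1 year more mean potential follow-up: a false difference of about 271 days per patient and a false-positive rate of 93%.
- Two years more: about 513 days and about 100%.

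**The case against.** The strongest defence is that the two measures answer different questions. The ratio describes hospital burden while alive, the total penalises death at equal follow-up, and mortality and MACE are reported beside them. In the group example with unequal rates, B scores higher because its hospital time while alive really is lower. This stands, and it is why the ratio may remain as a description. It does not make the ratio fit to show treatment benefit.

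An unseen full protocol or SAP could fix a horizon or person-time handling for the total. That also stands. It does not excuse the ratio, whose denominator is written down.

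A reader might infer three stronger things that the article does not support:

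- **That early deaths generally improve the score.** They do so only when enough time out of hospital precedes death; step 2 shows cases on both sides. The 50% mortality carries no time point and so says nothing about early deaths.
- **That calendar time drives the comparison of totals.** Between-arm bias needs entry dates to differ by arm, and no such dates are given. The 13-fold range rests on an assumed cut-off.
- **That neither measure can reflect treatment benefit.** At equal follow-up the total does.

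**Conclusion.** The point holds for the ratio by its own definition: days lost to death carry no penalty, and a patient who dies early out of hospital can outscore a long survivor. The direction follows from the denominator alone; the sizes (90% against 86% as defined, 1.5% against 86% over five years) rest on the chosen hospital days.

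For the total, the finding is conditional. It lacks a stated horizon in a registry with 9 to 17 years of entry, and it would mislead if follow-up is unequal and the arms differ in entry dates. Whether they do cannot be seen from the article.

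The consequence is limited to one of many secondary endpoints. The definition should be changed, but the primary endpoint and the mortality analysis are untouched.

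**What to change.** In Section 2.3, and in matching words in Section 2.2.2:

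- Make the between-group comparison days alive and out of hospital within fixed horizons, for example 1 year, and 5 years where follow-up allows.
- Use the horizon length as the denominator for every patient and count days after death as zero.
- Handle patients whose potential follow-up is shorter than the horizon by inverse-probability-of-censoring weights rather than exclusion, and apply the same IPTW as in the main analysis.
- Keep the days-alive ratio only as a descriptive measure of hospital burden while alive, labelled as no evidence of treatment benefit.

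The change needs rewording and minor programming; death and admission data are already collected. The price is precision at the longer horizon. With the assumed cut-off of 31 December 2023 and uniform entry, patients treated after 2018 lack 5 years of potential follow-up: 4.25/9.24 = 46% of entrants. Excluding them would be costly, hence the weights. The weights in turn assume that, given the covariates, late entrants would fare like earlier ones, and this should be stated.
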